## Abstract

**Background:**

The seemingly simple tasks of standing and walking require continuous integration of complex spinal reflex circuits between descending motor commands and ascending sensory inputs. Spinal cord injury greatly impairs standing and walking ability, but both improve with locomotor training. However, even after multiple locomotor training sessions, abnormal muscle activity and coordination persist. Thus, locomotor training alone cannot fully optimize the neuronal plasticity required to strengthen the synapses connecting the brain, spinal cord, and local circuits and potentiate neuronal activity based on need. Transcutaneous spinal cord (transspinal) stimulation alters motoneuron excitability over multiple segments by bringing motoneurons closer to threshold, a prerequisite for effectively promoting spinal locomotor network neuromodulation and strengthening neural connectivity of the injured human spinal cord. Importantly, whether concurrent treatment with transspinal stimulation and locomotor training maximizes motor recovery after spinal cord injury is unknown.

**Methods:**

Forty-five individuals with chronic spinal cord injury are receiving 40 sessions of robotic gait training primed with 30 Hz transspinal stimulation at the Thoracic 10 vertebral level. Participants are randomized to receive 30 min of active or sham transspinal stimulation during standing or active transspinal stimulation while supine followed by 30 min of robotic gait training. Over the course of locomotor training, the body weight support, treadmill speed, and leg guidance force are adjusted as needed for each participant based on absence of knee buckling during the stance phase and toe dragging during the swing phase. At baseline and after completion of all therapeutic sessions, neurophysiological recordings registering corticospinal and spinal neural excitability changes along with clinical assessment measures of standing and walking, and autonomic function via questionnaires regarding bowel, bladder, and sexual function are taken.

**Discussion:**

The results of this mechanistic randomized clinical trial will demonstrate that tonic transspinal stimulation strengthens corticomotoneuronal connectivity and dynamic neuromodulation through posture-dependent corticospinal and spinal neuroplasticity. We anticipate that this mechanistic clinical trial will greatly impact clinical practice because, in real-world clinical settings, noninvasive transspinal stimulation can be more easily and widely implemented than invasive epidural stimulation. Additionally, by applying multiple interventions to accelerate motor recovery, we are employing a treatment regimen that reflects a true clinical approach.

**Trial registration:**

ClinicalTrials.gov NCT04807764. Registered on March 19, 2021.

**Supplementary Information:**

The online version contains supplementary material available at 10.1186/s13063-023-07193-4.

## Administrative information

Note: the numbers in curly brackets in this protocol refer to SPIRIT checklist item numbers. The order of the items has been modified to group similar items (see http://www.equator-network.org/reporting-guidelines/spirit-2013-statement-defining-standard-protocol-items-for-clinical-trials/).

## Introduction

### Background and rationale {6a}

Spinal cord injury (SCI) is a long-term disability that greatly impacts quality of life for nearly 27 million people globally, and about 300,000 individuals in the USA [1, 2]. Restoration of motor function and especially stepping ability is of high priority for individuals with SCI wanting to improve functional independence and enhance quality of life [3]. In addition to the clinical sequelae of paresis and ambulatory dysfunction, SCI manifests as defects in multiple neurophysiological biomarkers, including but not limited to cortically induced motor evoked potentials (MEPs) and spinally induced Hoffmann (H) reflexes [4, 5]. MEPs provide information on the integrity of synaptic connections between the brain and spinal cord, while H reflexes provide information regarding spinal reflex excitability and function of complex spinal neuronal networks necessary for human movement. After SCI, MEPs have significantly delayed onsets, decreased amplitudes, and increased thresholds [4, 6]. SCI also hinders the ability of descending volleys to summate at the spinal cord and limits the electrophysiological transmission of uninjured axons [7, 8]. Damage to spinothalamic and dorsal column circuits disrupts transmission from receptors registering muscle stretch and cutaneous sensation [9]. These disruptions in the function and neurotransmission of uninjured fibers clearly demonstrate that SCI induces pathophysiology in the central nervous system beyond the immediate area of damage [10–14]. Consequently, interventions that effectively promote appropriate neuromodulation of spinal locomotor networks and strengthen connectivity of distributed neuronal networks across the neural axis are greatly needed.

Non-invasive rehabilitation strategies that restore or improve the ability of stepping have gained substantial interest in the research and clinical communities [15–17]. One of the most prevalent rehabilitation strategies is body weight support (BWS) step training with either manual or robotic assistance of leg movements. This strategy utilizes movement-induced afferent feedback to promote activity-dependent neuronal reorganization of neuronal networks after SCI. Afferent feedback, and the spinal reflex circuits integrating afferent feedback, is an essential source of the locomotor control scheme that alters the action of spinal locomotor networks to refine and coordinate the activity of different muscles across joints and between limbs during stepping [18, 19]. This is evident with the phase-dependent modulation of muscle and cutaneous reflexes that facilitate stepping such as the soleus H- and stretch-reflexes and the tibialis anterior (TA) flexion reflex [10, 20–23]. The important role of afferent feedback to spinal locomotor network function is further supported by the phase-dependent modulation of primary afferent depolarization and presynaptic inhibition of afferent feedback [24, 25]. SCI disrupts the phase-dependent modulation of the soleus H-reflex during walking [10], while the most common change observed with BWS-assisted step training is the partial return of soleus H-reflex depression during the swing phase [26]. Additional changes include restoration of soleus H-reflex rate-dependent or homosynaptic depression, recovery of spinal inhibitory circuits and spinal reflex excitability, and a more physiological intralimb and interlimb muscle coordination [27, 28]. These changes are likely linked to the normalization of the proportion of excitatory and inhibitory synaptic inputs to spinal motoneurons [29, 30], improvements in synaptic inputs from Ia afferents [31], and alterations in the concentration of neurotransmitters [32].

Transcutaneous spinal cord (transspinal) stimulation over the thoracolumbar region is a non-invasive, cost-effective method to produce neuromodulation across broad spinal neural networks. Transspinal stimulation facilitates recovery of motor, including locomotor, function after SCI [33, 34], increases the excitability of the spinal networks deprived of descending input, and enhances their responsiveness to input from residual intact descending pathways and afferent feedback [35]. Of clinical importance, transspinal stimulation enables the activation of spinal locomotor networks, aids in the generation of step-like muscle activity [36, 37], increases the net motor output [33], and reduces hyperreflexia [38–40] in individuals with SCI. The specific neuromodulation mechanisms likely incorporate the excitation of posterior root afferents which transsynaptically activate spinal locomotor networks, including spinal interneurons and motoneurons. Interestingly, transspinal evoked potentials (TEPs) and proprioceptive reflexes share similar neurophysiological properties [41–43]. For example, soleus H-reflexes and soleus TEPs are susceptible to rate-dependent homosynaptic depression when single stimuli at low frequencies are used, and when pairs of transspinal stimuli are delivered at short interstimulus intervals [42, 44]. Furthermore, TEPs recorded from the soleus muscle are depressed by Achilles tendon vibration and activation of the antagonist tibialis anterior (TA) muscle [45], and are modulated in a similar phase-dependent pattern in individuals with and without SCI during stepping [43, 46]. Together, these findings suggest that TEPs are conveyed by similar neuronal pathways to those used by the soleus H-reflex.

Locomotor training has been coupled with transcranial and/or transspinal direct current stimulation [47–49]. Studies have assessed the simultaneous combination of transspinal stimulation during locomotor training [40, 50–52]. In other contexts, such as upper extremity training after stroke, stimulation to the cortex applied prior to exercise may act as a “primer” to increase the neuroplastic response to exercise [53, 54]. The synergistic use of transspinal stimulation to prime locomotor training is a novel rehabilitation approach with significant clinical importance. In this randomized clinical trial, we test the effects of priming locomotor training with transspinal stimulation to maximize improvements in standing and walking ability in response to 40 sessions of therapy.

### Objectives {7}

The overall objective of this mechanistic randomized clinical trial is to use transspinal stimulation over the thoracolumbar enlargement, the spinal location of leg motor circuits, to prime locomotor training and ultimately improve the ability to stand and walk in individuals with chronic incomplete SCI. We hypothesize that non-invasive thoracolumbar transspinal stimulation administered before locomotor training increases neuronal responsiveness over multiple spinal segments, mechanistically reflected by increased responses to motor cortex stimulation, and improved phase-dependent modulation of spinal reflexes during walking. Because transspinal stimulation facilitates anti-gravity neuronal circuits, we further hypothesize that transspinal stimulation delivered while participants stand will augment gains compared to delivery in the supine position. To meet our overall objective, 45 individuals with incomplete SCI will undergo 40 sessions of BWS step training primed with 30 Hz transspinal stimulation. Participants are randomized to receive transspinal stimulation during standing (active or sham) or while supine (active).

Our *specific objective 1* determines whether priming locomotor training with transspinal stimulation strengthens corticomotoneuronal connectivity through posture-dependent corticospinal neuroplasticity, as reflected by increased MEP amplitudes and phase-dependent MEP amplitude modulation during stepping. We hypothesize that active but not sham transspinal stimulation delivered during standing increases MEP amplitudes and improves phase-dependent MEP amplitude modulation during stepping. We further hypothesize that transspinal stimulation delivered while supine increases MEP amplitudes but does not induce phase-dependent MEP amplitude modulation during stepping.

Our *specific objective 2* determines if priming locomotor training with transspinal stimulation evokes appropriate neuromodulation of spinal locomotor networks, as reflected by restored spinal inhibition, reduced neurophysiological hyperreflexia, and re-established phase-dependent soleus H-reflex modulation during stepping. We hypothesize that active but not sham transspinal stimulation delivered during standing (1) restores soleus H-reflex rate-dependent depression, (2) increases the depth of reciprocal inhibition between ankle extensor and flexor muscles, and (3) improves soleus H-reflex phase-dependent modulation towards a more physiological pattern during stepping. We further hypothesize that rate-dependent soleus H-reflex depression and soleus H-reflex modulation during assisted stepping recovers more in the transspinal-standing group than in the transspinal-supine group.

Our *specific objective 3* determines if priming locomotor training with transspinal stimulation improves the ability to stand and walk. Comparing locomotor electromyography (EMG) activity patterns before and after therapy will measure reorganized motoneuron activity and return of reciprocal activation between antagonistic muscles supporting intralimb and interlimb coordination. We hypothesize that the number of motor modules increases in the transspinal-standing group, and that antagonistic muscles show more reciprocal inhibition during stepping.

Our *specific objective 4* establishes clinically functional gains in motor and autonomic function. Improvements in walking ability are assessed with the 10-m test, 2-min test; improvements in balance ability are assessed with the BESTtest. Improvements in bowel, bladder, and sexual function are assessed with questionnaires. Clinical outcomes will be correlated with neurophysiological outcomes to identify predictors of recovery that can be based both on electrophysiological biomarkers and clinical assessment outcomes.

Upon conclusion, this clinical trial will indicate that priming locomotor training with transspinal stimulation improves the ability to stand and walk by facilitation and better synchronization of spinal locomotor neuronal networks and reflex circuits subserving standing and walking. This finding will support that transspinal stimulation works in parallel and not antagonistic to exercise, and can constitute a new standard of care for people with chronic SCI.

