### Trial design {8}

This is a mechanistic, sham-controlled, randomized, parallel design, multi-site (2 sites), clinical trial in which participants with chronic SCI are assigned in equal ratios to one of three study groups (or arms). Group 1: Active transspinal stimulation while standing followed by locomotor training; Group 2: Active transspinal stimulation while lying supine followed by locomotor training; and Group 3: Sham transspinal stimulation while standing followed by locomotor training. Study outcomes are assessed for superiority before (baseline) and after 40 sessions of primed locomotor training.

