The soleus H-reflex amplitude during assisted stepping in 11 persons with motor incomplete SCI (AIS C-D) recorded from the right leg was compared before and after locomotor training [26]. Based on the amplitude of the soleus H-reflex at mid-stance before and after training (difference in means of pre versus post: 13.67, pooled standard deviation: 17.4), the effect size was 0.79. To predict sample size at a power of 0.80 at α = 0.05 using a one-way ANOVA across 3 groups, 21 total subjects are needed. We will enroll 45 subjects, so we will be adequately powered even if subjects drop out at a higher than expected 20% rate.

Limb coordination relies on the strength of reciprocal inhibition between antagonistic muscles. We used data from a study performed by our group that examined short-latency inhibition from ankle flexor afferents onto ankle extensor motoneurons at rest in 13 persons with AIS C-D SCI before and after locomotor training [28]. Based on the amplitude of the conditioned H-reflex at the conditioning-test interval of 2 ms before and after training (difference in mean of pre versus post: 15.04, pooled standard deviation: 17.21), the effect size was 0.874. To predict sample size at a power of 0.80 at α = 0.05 using a one-way ANOVA across 3 groups, 18 total subjects are needed. We will enroll 45 subjects, so we will be adequately powered even if subjects drop out at a higher than expected 20% rate. Please note that the established power was based on data from SCI subjects who received either transspinal stimulation or locomotor training separately and not combined.

*Aim 3*: Determine if priming locomotor training with high-frequency transspinal stimulation improves limb coordination and the ability to stand and walk. These are secondary measures, and the study is not powered based on these outcomes.

Collectively, an average of 6 to 8 subjects per group is needed to establish significant differences for primary outcomes before and after transspinal stimulation or locomotor training. By enrolling 15 participants per group, the study will be robustly over-powered to detect these differences despite a projected possible 20% dropout rate, sporadic missing data values, or lower-than-expected observed effect sizes.

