## Statistical methods

### Statistical methods for primary and secondary outcomes {20a}

For each dependent variable (primary and/or secondary outcome), descriptive statistics including frequencies and percentages for categorical variables and means and percentile distributions for continuous variables to examine the distribution of outcomes and describe the study population are performed.

We will group each dependent variable based on the time of testing (before and after the intervention) and the subject group (2 experimental, 1 sham). A two-way mixed analysis of variance (ANOVA) along with Bonferroni post hoc* t-*tests [93] at 2 3 levels (2: time, 3: groups) to test the main and interaction effects among subject groups and time will be performed separately for each outcome. Furthermore, repeated measures analysis of covariance (ANCOVA) will be performed for each outcome separately with gender, age, level of SCI, and clinically evaluated baseline walking function as separate covariates. Outcomes will not be analyzed based on SCI severity because the ISNCSCI scale does not correlate with improvements in walking ability [3], while age is considered one of the predictors of ambulation in SCI [94].

Mixed regression methods and analysis of slope and threshold of correlation will be used to establish the relationship between the ability to stand and walk, quality of life, and changes in primary outcomes (neurophysiological biomarkers). We will use an identity or log link based on the data distribution.

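### Key hypotheses, the superiority sentence and the sample-size conclusion are worded as before–after changes within arms, although training alone should change every arm and the supine arm has no posture-matched sham

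*Protocol article*

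**What the plan says.** Objectives {7} predicts for objective 1 "We hypothesize that active but not sham transspinal stimulation delivered during standing increases MEP amplitudes", and for the supine arm that "transspinal stimulation delivered while supine increases MEP amplitudes but does not induce phase-dependent MEP amplitude modulation during stepping". Objective 2 repeats the pattern: "We hypothesize that active but not sham transspinal stimulation delivered during standing (1) restores soleus H-reflex rate-dependent depression". The same section also contains comparisons between arms. Standing delivery is expected to give larger gains than supine delivery, and rate-dependent depression and stepping modulation of the H-reflex are expected to be such that each "recovers more in the transspinal-standing group than in the transspinal-supine group".

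Trial design {8} defines Group 1 (active, standing), Group 2 (active, supine) and Group 3 (sham, standing), and adds: "Study outcomes are assessed for superiority before (baseline) and after 40 sessions of primed locomotor training". Sample size {14} sizes Aim 1 on a within-between interaction, but concludes that an average of "6 to 8 subjects per group is needed to establish significant differences for primary outcomes before and after" stimulation or training.

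Statistical methods {20a} plans "A two-way mixed analysis of variance (ANOVA) along with Bonferroni post hoc" t-tests, covering main and interaction effects of time and group, separately for each outcome. The Transspinal stimulation text under Intervention description {11a} names two comparisons: standing versus supine, and active versus sham during standing.

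**The concern.** All three arms receive the same 40 sessions of robotic gait training. A before–after change in an active arm, or a main effect of time, is therefore expected even if stimulation adds nothing. A significant change in one arm and a non-significant change in another is not a test of the difference between them.

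The supine hypothesis is the most exposed. It names no comparator, the only sham arm stands, and half of it predicts an absence of effect, which a non-significant result in a small arm cannot establish. Judged as worded, it would credit training gains to stimulation. The protocol expects its results to support a new standard of care, so what counts as evidence of a stimulation effect needs to be unambiguous.

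**Working it through.** **1. The plan's own figures.** Standardized changes from Sample size {14}: 148.05/206.8 = 0.716; 25.28/28.92 = 0.874; 13.67/17.4 = 0.786; 15.04/17.21 = 0.874.
- Aim 1, interaction F-test with three groups and two times: f = 0.716/2 = 0.358, correlation ρ = 0.5 (assumed; not stated), λ = f²·N·2/(1−ρ) = 0.128 × 24 × 4 = 12.3. Power is 0.839 at N = 24, matching the stated 24.
- Aim 2, one-way ANOVA with the standardized change entered as f: N = 18 (0.858), 21 (0.850), 18 (0.858), matching the stated 18, 21 and 18.

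The totals reproduce. Every input is a single-group before–after change; none is an active-minus-sham difference. The 0.786 and the second 0.874 come from locomotor training alone.

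**2. Chance of a false claim if separate within-arm tests decided.** Suppose both standing arms truly change by 0.79 SD and stimulation adds nothing. The paired-test effect is dz = 0.79/√(2(1−ρ)) = 0.79 at ρ = 0.5. Each arm is significant with probability p, from a noncentral t with n−1 df and noncentrality dz·√n (3.06 for n = 15; 2.74 for n = 12 = 15 × 0.8 after 20% dropout). The arms are independent, so P(active significant, sham not) = p(1−p).

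| n per arm | two-sided alpha | p | p(1−p) |
|---|---|---|---|
| 15 | 0.05 | 0.812 | 0.153 |
| 15 | 0.05/3 | 0.637 | 0.231 |
| 12 | 0.05 | 0.703 | 0.209 |
| 12 | 0.05/3 | 0.495 | 0.250 |

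The divisor 3 is an assumption, since the post hoc family is not stated. A valid test gives 0.025 in this direction. If neither arm changes, the rule gives 0.024 at alpha 0.05, so the excess comes from the shared training effect.

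Sensitivity, over the same n and alpha:
- ρ = 0.3: dz = 0.79/√1.4 = 0.668, range 0.22–0.25.
- ρ = 0.7: dz = 0.79/√0.6 = 1.02, range 0.04–0.19.
- Smaller shared change at ρ = 0.5, n = 15, alpha 0.05: 0.15 for 0.3 SD and 0.25 for 0.5 SD.

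**3. The same rule with the interaction required first.** I simulated three arms, each changing by 0.79 SD (400,000 trials), and required the group-by-time F-test (2 and 3n−3 df) to reach 0.05 before looking at the arms. The false-claim rate falls to 1.3–1.6%.

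**4. What each pair of arms isolates.**
- Group 1 vs Group 3: same posture, active versus sham. Stimulation only.
- Group 1 vs Group 2: both active. They differ in posture during stimulation and in the standing itself, nominally 40 × 30 min = 20 h, with body weight support and breaks.
- Group 2 vs Group 3: they differ in stimulation and posture together.

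**5. The predicted absence of modulation.** With a true change of 0.5 SD, a paired test at 0.05 has power 0.438 (n = 15) or 0.353 (n = 12), so it misses the change 56% or 65% of the time. The MEP outcomes also need an obtainable soleus MEP at baseline (Outcomes {12}), so 15 is an upper limit.

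**The case against.** A reader might infer that the hypotheses are to be judged by separate within-arm tests, or that the trial never tests stimulation at all. The documents support neither. No sentence makes within-arm significance the decision rule. The analysis section specifies a group-by-time interaction, Aim 1 is sized on one, Objectives {7} contains explicit standing-versus-supine comparisons, and Group 1 vs Group 3 is a randomized, posture-matched, sham-controlled comparison named in the intervention text. The superiority sentence can be read as giving assessment times, and the 'but not sham' wording as a directional prediction. Nor does the text say that the post hoc tests run over every pair of the six time-by-group cells.

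It is also fair that the deciding contrast and the post hoc family are commonly left to an analysis plan, which is not shown, and that upright posture is part of the treatment concept, so standing versus supine is a legitimate comparison of packages.

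All of that stands, and it makes the 15–25% conditional. It does not remove the wording. The hypotheses, the superiority sentence and the sizing conclusion are stated text, and they point to within-arm change while the valid tests lie elsewhere. Nor is an interaction gate complete protection for the sham comparison: if the interaction is significant because Group 2 differs, reading the standing arms one at a time returns towards the ungated rate.

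**Conclusion.** The concern holds in a limited form. The plan contains a valid test of stimulation in standing, but key claims are worded so that a training effect common to all arms could be read as a stimulation effect. The supine hypothesis cannot be attributed to stimulation by any comparison in this design.

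If the within-arm reading were used, the false-claim chance is about 15–25%, against about 2% with the interaction required first. This assumes an equal 0.79 SD change in both standing arms, ρ = 0.5, 12 to 15 per arm, and alpha of 0.05 or 0.05/3; at ρ = 0.7 it is 4–19%. The 0.79 is an H-reflex figure; the protocol gives no locomotor-only change for MEPs, so carrying the rate to objective 1 is a further assumption.

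**What to change.** Before allocation is disclosed for the between-group tests:
- Restate each hypothesis as a between-arm difference in change, decided by two prespecified contrasts: Group 1 vs Group 3 (stimulation effect in standing) and Group 1 vs Group 2 (stimulation posture together with the standing it entails). Control the two by Holm or a fixed sequence.
- Replace the 'but not sham' and 'does not induce' wording with between-arm differences.
- Report within-arm changes and the time main effect descriptively, with confidence intervals.
- Describe Group 2 vs Group 3 only as a combined stimulation-and-posture difference.
- Reword the superiority sentence and the sample-size conclusion to match.

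The cost is wording. Within-arm p-values no longer support efficacy, and the supine and posture claims become narrower. The change also exposes the power of the deciding contrast. Suppose active exceeded sham by the whole cited before–after effect, which is optimistic. With ρ = 0.5, 15 per arm and two-sided 0.05, the noncentrality is d·√(15/2) on 28 df, and power is 0.47, 0.55 and 0.64 for d = 0.716, 0.786 and 0.874. With 12 per arm it is 0.39, 0.45 and 0.54. The claim of being amply powered should then be confined to before–after change.

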### Methods for additional analyses (e.g., subgroup analyses) {20b}

There will be no additional analyses.

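### Objective 1 hypothesises that supine stimulation does not produce phase-dependent MEP modulation, but the plan contains only superiority tests, so no planned result can support that clause.

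*Protocol article*

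**What the plan says.** Under Objectives {7}, specific objective 1 makes two predictions for the supine arm: it "increases MEP amplitudes but does not induce phase-dependent MEP amplitude modulation during stepping". The same section has a general directional hypothesis, that "transspinal stimulation delivered while participants stand will augment gains compared to delivery in the supine position". Objective 2 puts its posture hypothesis for the soleus H-reflex directionally too, as greater recovery with standing than with supine delivery. Objectives 1 and 2 both also predict a response to active but not to sham stimulation.

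Trial design {8} sets the framework: "Study outcomes are assessed for superiority before (baseline) and after 40 sessions of primed locomotor training". Participants are "assigned in equal ratios to one of three study groups", and Sample size {14} gives 15 per arm with dropout projected at 20%. The analysis in section {20a} is "A two-way mixed analysis of variance (ANOVA) along with Bonferroni post hoc" t-tests over two times and three groups, "to test the main and interaction effects among subject groups and time will be performed separately for each outcome", with covariate-adjusted versions. Section {20b} adds: "There will be no additional analyses".

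Outcomes {12} lists MEP amplitude at mid-stance and mid-swing among the primary outcomes, for participants whose soleus MEPs can be obtained at baseline. Section {6b} says that all participants undergo the same locomotor training.

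**The concern.** A superiority test can reject the hypothesis of no difference; it cannot confirm it. The supine clause asserts an absence, yet the article gives no margin or confidence-interval criterion for it, sizes the trial only to detect differences, and excludes further analyses. A significant result would contradict the clause, and a non-significant one would leave it undecided.

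This goes beyond detail that an article may leave to a statistical analysis plan. The article itself pairs a no-effect hypothesis with a framework that cannot test it. What is at stake is one published statement: that supine stimulation does not produce phase-dependent modulation. Small arms and a Bonferroni adjustment both make non-significance more likely, so the data could appear to agree with the clause whether or not it is true.

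**Working it through.** **1. The plan's own figure.** Sample size {14}, Aim 1, gives a mean difference of 148.05, SD 206.8, d = 0.71 (148.05/206.8 = 0.716), and 24 participants in total for 80% power at α = 0.05 in a within-between interaction ANOVA with three groups. Take f = d/2 = 0.355, m = 2 measurements and correlation ρ = 0.5 (assumed). The noncentrality is λ = f²·N·m/(1−ρ), with 2 and N−3 degrees of freedom.
- N = 21: power 0.767.
- N = 24: λ = 0.126 × 24 × 2/0.5 = 12.1, power 0.833.

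The smallest balanced total is 24, as stated. This is a calculation for detecting a difference. No figure in the section concerns showing an absence.

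**2. The right comparison.** A before-after change in the supine arm combines 40 training sessions with the stimulation. Whether the stimulation induces modulation is therefore a between-arm question, supine versus sham, on the change score.

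**3. Inputs.** n = 15 per arm, or 15 × 0.8 = 12 after 20% dropout. Effects are in SD of the change. The article gives no effect size or SD for stepping MEPs, so two values are assumed: 0.71, borrowed from Aim 1 (resting tibialis anterior MEPmax in healthy subjects), and 0.5. With ρ = 0.5 and equal variances, the SD of the change equals the SD of a single measurement, so 0.71 carries over unchanged.

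**4. Precision.** The 95% half-width is t(0.975, 2n−2) × √(2/n).
- n = 15: 2.048 × 0.365 = 0.75 SD.
- n = 12: 2.074 × 0.408 = 0.85 SD.

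An estimate of exactly zero would exclude neither 0.5 nor 0.71 SD.

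**5. Miss rates.** Two-sample t-test with noncentrality d·√(n/2); the chance of a miss is 1 − power. The last two columns assume Bonferroni over three comparisons.

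| True difference | n = 15, α 0.05 | n = 12, α 0.05 | n = 15, α 0.05/3 | n = 12, α 0.05/3 |
|---|---|---|---|---|
| 0.71 SD | 53% | 62% | 71% | 78% |
| 0.5 SD | 74% | 78% | 86% | 89% |

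**6. What showing absence would take.** Two one-sided tests at 5%, true difference zero, 80% power: about 69 per arm for a 0.5 SD margin and 35 per arm for 0.71 SD. With 15 per arm the power is about 1% and 21%. These margins are illustrative.

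**The case against.** The strongest reply is that the clause is a scientific prediction rather than a decision rule. Nowhere does the article say that p > 0.05 will be taken as proof of no effect. A reader might infer that intention, since non-significance is the only planned result that could seem to agree with the clause, but the documents do not state it. Rules for interpreting null results may sit in a document not shown. This limits the point to a mismatch between hypothesis and framework; it does not remove the mismatch.

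A reader might also infer that the trial rests on tests in 15 participants. It does not: the mixed ANOVA uses all 45, and on the Aim 1 inputs its interaction test has power of about 0.99. That figure does not rescue the clause. With ρ = 0.5, f = 0.355 means that the arm mean changes have a standard deviation of 2 × 0.355 = 0.71 SD of change. If only the standing arm moves, it must differ from the other two by 0.71/(√2/3) = 1.51 SD. A non-significant interaction would not establish absence in the supine arm, and a significant one would not say that supine equals sham.

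Finally, a reader might conclude that posture dependence cannot be shown unless supine stimulation has no effect. That is too strong. Posture dependence needs only a difference between standing and supine delivery, and would hold if supine delivery had a smaller, non-zero effect. The group-by-time interaction and the standing-versus-supine contrast are valid superiority tests of it, and low power makes that conclusion harder to reach, not easier.

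**Conclusion.** The point stands, confined to the no-effect clause for the supine arm and, in the same form, to the active-but-not-sham predictions in objectives 1 and 2. No planned analysis can support those absences. A non-significant supine-versus-sham difference would be compatible with differences up to about 0.75 SD either side of the estimate (0.85 SD with 12 per arm), and would occur 53% to 78% of the time if the true difference were 0.71 or 0.5 SD, before any Bonferroni adjustment.

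The sizes depend on the assumed effects and on full arms of 15 or 12. Restricting the MEP analysis to participants with obtainable soleus MEPs could leave fewer. The logical point depends on none of these figures. The tests of posture dependence are not in question.

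Testing the supine arm's own before-after change against an equivalence margin would not repair the clause, because that change also contains the effect of training.

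**What to change.** In Objectives {7}, specific objective 1, replace the no-effect clause with a directional one: the change in phase-dependent MEP modulation is larger with standing-active than with supine-active stimulation. This matches the form already used in objective 2.

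In section {20a}, state that the standing-minus-supine and supine-minus-sham differences in change will be reported with 95% confidence intervals. A non-significant supine-versus-sham difference will be described as not shown, with its interval, and not as absence of effect. Apply the same reporting rule to the active-but-not-sham predictions, so that active stimulation is compared with sham directly and no absence of change under sham is claimed.

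The cost is the rewording of one clause and one reporting rule, with no new participants, measurements or data. The trial gives up the claim that supine stimulation has no effect on modulation, which 15 per arm could not have supported at the margins examined.
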